### **12.3. Populations to be analyzed:**

Three populations will be included in the analysis: i) the intention-to-treat (ITT) population comprising all patients randomized by their assigned treatment groups, ii) the per-protocol population comprising all ITT patients without any significant deviation from protocol, and iii) the safety population comprising all patients randomized and having received at least one dose of study treatment.

Descriptive statistics for demographic data and baseline characteristics will be presented for the per-protocol and ITT populations.

### **12.4. Efficacy analysis:**

For analysis of the primary outcome, a one-sided Fisher's exact test of the proportion of patients with a significant decrease in biomarker levels in the ITT (primary analysis) and per protocol (secondary analysis) populations will be used. ANOVA test will be performed to analyze differences in variances between the different markers. An exact test will be performed for all secondary comparisons of proportions between ATO versus placebo, including parasitological response to treatment. Latent class and multivariate analyses will assess the association between parasitological response, biomarker changes, and ATO doses.

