### Efficacy analysis:

**Hypothesis:** Atorvastatin, in combination with conventional antichagasic therapy of nifurtimox or benznidazole, improves cardiac function in subjects with asymptomatic chronic-phase Chagas disease compared with placebo.

For analysis of the **primary outcome**, a one-sided Fisher's exact test of the proportion of patients with a significant decrease in biomarker levels in the ITT (primary analysis), and per protocol (secondary analysis) populations will be used. ANOVA test will be performed to analyze differences in variances between the different markers.

An exact test will be performed for all secondary comparisons of proportions between ATO versus placebo, including parasitological response to treatment. Latent class and multivariate analyses will assess parasitological response, biomarker changes, and ATO dose association.

If there are no significant differences between ATO treatments, these data will be collapsed into a single comparison group to obtain greater precision in the treatment effect estimate, given that this is a proof-of-concept study for statins as a class. In this case, no adjustment for multiple comparisons will be made.

**Safety Analysis:** Clinical assessments, electrocardiograms, and laboratory tests will be used to monitor the safety and tolerability of the drugs under study throughout the observation period of the subjects.

The proportion of patients presenting at least one AE will be described. The incidence rate and 95% confidence interval per study group will be presented. Otherwise, only descriptive statistics will be presented. Laboratory safety parameters (hematology and biochemistry) will also be described individually for each study group, showing the proportion of patients by degree of elevation relative to ULN and to baseline values and changes in blood levels over time.

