## **8. OBJECTIVE AND GOALS OF THE TRIAL**

### **8.1. Primary Goal:**

To evaluate the use of atorvastatin, in combination with antiparasitic therapy (NFX or BZD), is safe and more effective than antiparasitic therapy alone in preventing the occurrence of cardiac disturbances by reducing overall inflammation and in improving endothelial and cardiac functions.

To assess the primary endpoint, the number of patients with a change in the stage of chronic cardiomyopathy in 12 months from the beginning of antichagasic treatment will be considered.

We will evaluate whether the effect of atorvastatin in combination with antiparasitic treatment (NFX or BZD) is more effective than antiparasitic therapy alone (placebo group) in preventing the appearance of cardiac disorders determined by non-progression from stage A according to the First Latin American Guidelines for the diagnosis and treatment of chagasic cardiomyopathy (Andrade et al, Arq Bras Cardiol 2011;97 Suppl 3:1-48.) To make this assessment, significant changes in i) electrocardiogram (heart rate and QT interval duration, as well as the appearance of electrical conduction disorders, determined by QRS segment duration and morphology), ii) ejection fraction

(assessed by echocardiography), and iii) cardiac silhouette size (chest X-ray) will be taken into account

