## 9. Study design:

### 9.1. Outcomes:

As in any clinical trial, the results should be clearly defined beforehand. Thus, the **primary outcome** of this study at 12 months is the change in cardiac function in patients with chronic CAD. To this end, the number or proportion of patients presenting a change in the phase of chronic cardiomyopathy will be assessed. This phase change is determined by non-progression or reversion from or to phase A, according to the I Latin American Guidelines for the diagnosis and treatment of chagasic cardiomyopathy (Andrade et al., 2011), considering the consistent findings of structural alteration evidenced by changes in clinical, electrocardiographic, echocardiographic parameters and, additionally, of plasma levels of the cardiac function biomarkers BNP, cTnT.

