|                                                             | A                                                                                                                                       | B1                                                                                                                                                                                                           | B2                                                                                                                                               | C                                                                                                        | D                                                                                                                           |
| Patients with findings compatible with acute Chagas disease | Patients at risk for developing CHF. They have positive serology, neither structural cardiopathy nor CHF symptoms. No digestive changes | Patients with structural cardiopathy, evidenced by electrocardiographic or echocardiographic changes, but with normal global ventricular function and neither current nor previous signs and symptoms of CHF | Patients with structural cardiopathy characterized by global ventricular dysfunction, and neither current nor previous signs and symptoms of CHF | Patients with ventricular dysfunction and current or previous symptoms of CHF (NYHA FC I, II, III or IV) | Patients with refractory symptoms of CHF at rest, despite optimized clinical treatment, requiring specialized interventions |

Arq Bras Cardiol 2011; 97(2 supl.3): 1-48

The **secondary outcome** is determined by the change in plasma levels of biomarkers versus changes in parasite load.

Additional measures of scientific value: (a) change in plasma levels of biomarkers of inflammation and endothelial activation; (b) incidence and severity of AEs; (c) change in parasite burden and serologic response over the follow-up period, measured by quantitative PCR (qPCR); (d) changes in biomarker levels at different follow-up time points and correlation with parasite burden and ATO regimen; and (e) incidence of treatment discontinuation due to severe AEs.

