### **12.Data analysis and statistical methods:**

#### **12.1. Sample size:**

A sample size of 75 patients per group is sufficient to achieve a power of 90% at an overall significance level of 5% (2-sided), assuming that the proportion of patients who improve electrocardiographic and echocardiographic parameters, as well as the levels of the cardiac function markers BNP and cTnT in the EOT in the experimental treatment group is 0.40. The proportion in the placebo group is 0.20, with an odds ratio of 2.5. Considering an estimated dropout rate of 25%, 100 patients per group (300 patients in total) would be recruited (Fleiss et al., 2003). The study will be sufficiently powered to provide evidence of the superior efficacy of either statin dose plus antichagasic therapy relative to antichagasic treatment alone.

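### The outcome declared primary, cardiomyopathy stage change at 12 months, has no test: the primary test goes to a biomarker decrease, and the sample size to a third, related definition

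*Protocol*

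**What the plan says.** Section 8.1 says that the primary endpoint is assessed by "the number of patients with a change in the stage of chronic cardiomyopathy in 12 months from the beginning of antichagasic treatment". Section 9.1 agrees: for the primary outcome at 12 months, "the number or proportion of patients presenting a change in the phase of chronic cardiomyopathy will be assessed". The stage is judged by the cited Latin American guideline on clinical, ECG and echocardiographic findings and, "additionally, of plasma levels of the cardiac function biomarkers BNP, cTnT".

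Section 12.4 reads: "For analysis of the primary outcome, a one-sided Fisher's exact test of the proportion of patients with a significant decrease in biomarker levels". The Summary's efficacy paragraph has the same test. In both places the remaining exact tests are reserved for secondary comparisons.

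Elsewhere biomarkers rank below primary. Section 8.2.1 puts all of them, including BNP and cTnT, under secondary goals. Section 9.1, after Chart 1, says that the secondary outcome "is determined by the change in plasma levels of biomarkers versus changes in parasite load", and it lists further biomarker changes as additional measures.

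Section 12.1 bases the sample size on a responder rate that counts "patients who improve electrocardiographic and echocardiographic parameters, as well as the levels of the cardiac function markers BNP and cTnT in the EOT", taken as 0.40 on experimental treatment and 0.20 on placebo.

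**The concern.** The sections that declare the primary outcome and the section that tests it name different variables. An analyst who followed 12.4 would report, as the primary result, a p-value for a quantity that 8.1 and 9.1 do not call primary, and would have no instruction for the quantity that they do. The sample size supports neither directly. A reader of the Summary alone would not learn that stage change is the declared outcome, because the Summary never states it.

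At stake is whether the trial's headline result answers its declared question, and whether anything is known about its power to do so.

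**Working it through.** **1. The definitions side by side**

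| Place | Role | Variable | Time |
|---|---|---|---|
| 8.1, 9.1 | Declared primary | Change of cardiomyopathy stage, judged on clinical, ECG and echo findings, plus BNP and cTnT | 12 months |
| 12.4, Summary | Primary test (one-sided Fisher) | Significant decrease in biomarker levels | Not stated |
| 12.1 | Sample size | Improvement in ECG, echo, BNP and cTnT | End of treatment |
| 8.2.1, 9.1 | Secondary or additional | Biomarker changes | Follow-up |

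The first two rows should match and do not. No test in 12.4 is attached to stage change.

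**2. Can the definition in 12.1 be measured when it says?** The schedule in 9.6 has the 2D echocardiogram at screening and day 360 only. Antichagasic treatment takes about 60 days and the washout 14, so atorvastatin starts at about day 60 + 14 = 74, or later if liver enzymes have not normalised. The protocol gives two durations for atorvastatin or placebo, which must be reconciled:
- two months (Summary; eight weeks in 9.5): 74 + 56 = day 130
- four months (9.3): 74 + 120 = day 194

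Neither is near day 360, and 9.5 itself places day 360 after end of treatment. There is no echocardiogram at days 60, 120 or 180. The echo component therefore cannot be assessed at end of treatment.

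**3. Can 0.40 against 0.20 describe stage change?** Section 10.1 admits only patients in the indeterminate phase, which is stage A, the lowest chronic stage in Chart 1.
- As improvement: nobody starts above A, so no patient can improve in stage from baseline.
- As non-progression: the rates would mean that 1 − 0.40 = 60% of treated and 1 − 0.20 = 80% of placebo patients progress within 12 months. Section 9.2 says that clinical events are infrequent in indeterminate disease.
- As progression: the experimental arm would do worse.

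No reading carries these rates over to the declared outcome.

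**4. The plan's own figure.** With p1 = 0.40, p2 = 0.20, mean 0.30, two-sided 5% and 90% power:

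n = [1.960·√(2·0.30·0.70) + 1.2816·√(0.40·0.60 + 0.20·0.80)]² / 0.20² = (1.270 + 0.811)² / 0.04 ≈ 108.2, so 109 per group (119 with continuity correction).

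The stated 75 is not reproduced. The dropout step is: 75 / (1 − 0.25) = 100. The shortfall is a separate matter and this point does not depend on it.

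**5. Power for the declared outcome.** The protocol gives no stage-change rate, so none can be computed. As an illustration on assumed 12-month progression rates, with 75 per group and a one-sided exact Fisher test at an assumed 5% level:

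| Placebo | Atorvastatin | Power |
|---|---|---|
| 2% | 1% | 1% |
| 5% | 2.5% | 8% |
| 10% | 5% | 23% |
| 5% | 0% | 32% |

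**6. Biomarker sampling.** Samples are scheduled on days 0, 60, 120 and 360. On the timings in step 2, day 120 falls during atorvastatin under either duration. Day 360 is the only scheduled sample after it ends.

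**The case against.** The strongest defence is that the definitions are facets of one idea. Section 9.1 brings BNP and cTnT into the judgement of stage, so the biomarkers in 12.4 could mean those two, and the composite in 12.1 uses nearly the same components as 9.1. The aim in 8.1 also mentions reduced inflammation. Part of this stands: 12.1 is related to 9.1 rather than foreign to it, and it would be wrong to speak of three unrelated endpoints. But a fall in BNP is not a stage change, 9.1 adds those markers only as a further consideration, and 8.2.1 ranks both as secondary.

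A second defence is that an analysis plan, not shown here, may settle the matter. That excuses missing detail, such as which markers must fall and by how much, and no criticism is made of that. It does not excuse 12.4 for assigning the primary test to a variable other than the declared one.

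A reader might infer more than the documents support:
- That the false-positive rate is inflated by a calculable amount. Section 12.4 states no significance level, nothing says that all definitions will be tested, and they are clearly correlated.
- That the sponsor could pick the endpoint after unblinding. An analysis plan could fix it beforehand.
- That the stage outcome is incapable of changing. Stage A can progress; 9.2 implies that this is infrequent, not impossible.

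**Conclusion.** The contradiction is real and is wrong as written: 8.1 and 9.1 declare stage change at 12 months as primary, while 12.4 and the Summary give the primary test to a biomarker decrease and leave stage change without one. This rests on the protocol's wording alone.

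Section 12.1 adds a mismatch in definition and time point. Its composite shares components with 9.1, but its echo part cannot be assessed at end of treatment under the schedule, and its improvement rates cannot describe stage change in patients who all enter at stage A.

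The effect on power for the declared outcome cannot be sized from the documents. The illustrative 1% to 32% depends entirely on assumed rates and an assumed one-sided 5% level.

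**What to change.** Choose one primary variable, one visit and one comparison, including sidedness (12.1 is two-sided, 12.4 one-sided), and state it identically in the Summary, 8.1, 9.1, 12.1 and 12.4.

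The default is to keep the outcome already declared: have 12.4 and the Summary test stage change at day 360, say which result counts as success, make biomarker decrease secondary, and restate the rates and power in 12.1 for that outcome. ECG, echocardiogram, chest X-ray and biomarkers are already scheduled at day 360, so no visit is added.

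The cost is an amendment and a new sample-size justification. The stated power may become less favourable, because events are described as infrequent and a stage-change rate must be found or assumed; the number of patients may change.

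The sponsor may prefer another endpoint. If a biomarker becomes primary, day 360 is the only scheduled sample after atorvastatin ends, and an earlier post-treatment reading needs added sampling. If the composite in 12.1 is kept, it must move to day 360 or an echocardiogram must be added at end of treatment. Either choice also needs 8.1 and 9.1 rewritten and 12.1 re-derived for the chosen variable.

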#### **12.2. Randomization and treatment allocation:**

A computer-generated randomization list will be prepared and stratified by center using a block size of twelve. Each center will receive a list of randomization numbers and corresponding ATO or placebo packages. After patient enrollment, the following randomization number available at the

center will be assigned (in chronological order), and the corresponding treatment package will be delivered.

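### The trial is sized at a two-sided 5% level, but the primary test is one-sided with no level given, so the primary type I error is not defined

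*Protocol*

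**What the plan says.** Section 12.1 (Sample size) states the design at "A sample size of 75 patients per group is sufficient" for 90% power, "at an overall significance level of 5% (2-sided"). The assumed rates are 0.40 with atorvastatin and 0.20 with placebo.

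Section 12.4 (Efficacy analysis) names the primary test as "a one-sided Fisher's exact test of the proportion of patients", with ITT as the primary population and per protocol as the secondary one. The Efficacy analysis part of the Summary repeats it: "a one-sided Fisher's exact test of the proportion of patients with a significant decrease in biomarker levels". Neither place gives a significance level for the test. The 5% in section 12.1 is the only significance level in the protocol.

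Section 12.2 describes the randomisation as "stratified by center using a block size of twelve". Section 12.4 names a plain Fisher test and does not mention centre.

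**The concern.** A two-sided 5% level allows 2.5% for a false claim in favour of atorvastatin. A one-sided test has no such allowance until its level is stated. Someone who applies the protocol literally would take the one-sided test from section 12.4 and the 5% from section 12.1, and would so double the allowance. Someone who holds to section 12.1 would not.

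The two readings disagree on a band of plausible results, so the protocol can be cited both for and against the same claim of success. The one-sided test appears in two places, so it is unlikely to be a single slip. A statistical analysis plan could not settle the matter without overriding one of the protocol's own statements. If that choice were made after the data were seen, it would be open to challenge.

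**Working it through.** **Inputs.** From section 12.1: 75 evaluable per group, 0.40 against 0.20, 90% power, two-sided 5%. From section 12.4 and the Summary: Fisher's exact test, one-sided, level not given. All figures below are for one dose against placebo, 1:1.

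**1. The plan's own figure.** The usual formula for two proportions is

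n = [z(1−α/2)·√(2p̄(1−p̄)) + z(1−β)·√(p₁(1−p₁) + p₂(1−p₂))]² / (p₁−p₂)².

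With p̄ = 0.30 the two roots are √0.42 = 0.648 and √0.40 = 0.632.

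- Two-sided 5%, 90% power: (1.960 × 0.648 + 1.282 × 0.632)² / 0.04 = 108.2, so 109 per group (119 with continuity correction, 117 by exact Fisher).
- One-sided 5%, 90% power: (1.645 × 0.648 + 1.282 × 0.632)² / 0.04 = 88.0, so 89 per group (98 with continuity correction, 97 by exact Fisher).

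The stated 75 is not reproduced under either sidedness, so it does not show which level was meant.

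**2. Nominal error in favour of atorvastatin.**

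- Two-sided 5%: 0.05 / 2 = 2.5%.
- One-sided 5%: 5%, which is twice as much.
- One-sided 2.5%: 2.5%, which is the same as two-sided 5%.

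**3. Exact size and power of Fisher's test at 75 against 75.** Every pair of binomial outcomes was enumerated. Size is taken in the favourable direction at a common rate of 0.20, and power at 0.40 against 0.20.

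| Reading | Size in favour of atorvastatin | Power |
|---|---|---|
| One-sided 5% | 3.3% | 80.9% |
| Two-sided 5% | 1.5% | 71.4% |
| One-sided 2.5% | 1.5% | 71.4% |

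**4. Results on which the readings disagree.** Placebo is held at the planned 20%.

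| Atorvastatin v placebo | One-sided p | Two-sided p |
|---|---|---|
| 25/75 v 15/75 | 0.048 | 0.096 |
| 26/75 v 15/75 | 0.033 | 0.066 |
| 32/100 v 20/100 | 0.038 | 0.076 |
| 33/100 v 20/100 | 0.027 | 0.054 |

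Each row is a success at one-sided 5% and a failure at two-sided 5%. The rows with 100 per arm apply if all randomised patients are analysed.

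**5. Does leaving out centre change the error rate?** The size of the unstratified one-sided 5% Fisher test was computed at 75 per arm, with allocation balanced within four centres and no treatment effect. The centre rates are assumptions.

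| Assumed centre rates | Size |
|---|---|
| All 0.20 | 3.3% |
| 0.10 to 0.30 | 3.0% |
| 0.05 to 0.40 | 2.5% |
| 0.02 to 0.50 | 1.7% |

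The size falls as the centres diverge, so omitting centre makes the test more conservative.

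**The case against.** The strongest reply is that one-sided 2.5% may be what was intended. That test has the same favourable-direction size and the same power as the two-sided 5% Fisher test (step 3), and it would agree with section 12.1. This stands as far as it goes. A reader might infer that the trial will run at a different error rate from the one it states, but the protocol does not establish that. What it establishes is that the level of the primary test is missing and that the two stated parts do not fit together. The doubling follows only if 5% is applied one-sided.

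It can also be said that doubling overstates the practical risk. Because Fisher's test is conservative, the actual size at the planning rate is 3.3% even at one-sided 5%. That is true, but it is still about twice the 1.5% under the two-sided level, and the disagreements in step 4 are unaffected.

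Three further readings are tempting, and the document does not support them:

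- **That 75 per group reveals a one-sided 5% plan with 80% power.** With continuity correction that combination gives 74. One-sided 5% with 90% power also gives 74 controls if the two atorvastatin arms are pooled 2:1, and the Summary provides for such pooling. How 75 was derived cannot be recovered.
- **That ignoring centre makes the error rate wrong.** Step 5 shows the opposite direction. Adjustment for centre is also commonly left to a statistical analysis plan, which is not at hand.
- **That ignoring centre costs the difference between 77% and 71% power.** Neither figure involves centre. The first is the normal-approximation test and the second is Fisher's test, both at two-sided 5%, so the gap comes from Fisher's discreteness.

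Fisher's test is a valid choice for two proportions and need not be replaced to cure the inconsistency.

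**Conclusion.** The point holds in this form: section 12.1 and section 12.4 (with the Summary) are inconsistent on sidedness, and the level of the primary test is undefined. This needs correcting, because the protocol's own statements reach opposite conclusions for results with two-sided p between 0.05 and about 0.10.

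The size of the problem depends on the missing level. If 5% is applied one-sided, the nominal favourable error is twice that implied by section 12.1; if one-sided 2.5% was meant, it is unchanged. The exact figures assume 75 per arm, a 20% rate under no effect, and a single dose-against-placebo comparison. The contradiction itself rests on no assumption and can be read directly from the text.

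**What to change.** State one sidedness and one level, in the same words, in section 12.1, section 12.4 and the Summary: two-sided 5%, or explicitly one-sided 2.5%. Add that the primary result will be reported with an effect estimate (risk difference or odds ratio) and a 95% confidence interval. Make the change by amendment before unblinding.

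The text change is a sentence or so in each place. The statistical cost is a stricter threshold than one-sided 5%: at 75 per arm and 0.40 against 0.20, Fisher power is 71.4% instead of 80.9%. Either figure is below the 90% claimed, so the sample size statement should be recomputed once the level is fixed.

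Optionally, stratify the primary test by centre to match the randomisation. This may improve precision, but it does not correct the error rate.

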### 9.7. Assessments:

On admission to the PCC, patients will undergo a complete medical history with an emphasis on CD, demographic data and medication history, physical examination, body weight and height, vital signs, and body temperature.

Ten ml of blood will be collected, in separate tubes, for hematological and biochemical evaluations: hemoglobin, total and differential white blood cell count, platelet count, CK, ALT, AST, GGT, alkaline

phosphatase, total and direct bilirubin, a lipid profile: total cholesterol, c-HDL, and c-LDL, triglycerides, fasting blood glucose and creatinine. A serum pregnancy test will also be performed. This test will be performed in the clinical laboratories of each center.

A 3 mL blood sample will be collected for conventional CD serology at each center's clinical laboratories and for a confirmatory serology test to be performed at the ISPCCH or an accredited laboratory.

5 mL of blood will be collected for qPCR. For clinical development and proof of concept, it has been proposed to use quantitative PCR parasitological tests as markers of efficacy in clinical studies of chronic indeterminate CD (Parrado et al., 2019). Thus, the real-time PCR technique described by Duffy et al. will be used in this assay (Duffy et al., 2013). Blood samples will be immediately added to a tube containing a volume (10mL) of a solution of guanidine/CIH 6M EDTA 0.2M 0.2M guanidine/CIH buffer 0.2M pH 8.0 (GEB) (Schijman et al., 2003). Samples with guanidine buffer can remain at room temperature for up to 30 days. For longer periods, it is necessary to store them in a refrigerator. After DNA extraction, samples will be processed using a commercial kit on an Applied 155 Biosystems 7300 RT-PCR system (Thermo Fisher).

An additional 3 ml of blood will be drawn for the biomarkers: BNP, cTnT, IFN- $\gamma$ , IL-1 $\beta$ , IL-4, IL-17A, and IL-10, sICAM-1, sVCAM-1, sE-selectin. These markers were selected following a literature review (Cortes-Serra et al., 2020; Echeverría et al., 2020; Llaguno et al., 2019). Serum levels of these markers will be determined using a multiplex approach with a Luminex 200 (R&Dsystems). To establish biological reproducibility, a pilot study will be performed before the sample analyses of this assay.

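### Section 12.4 tests continuous plasma biomarker levels through an undefined yes/no decrease with Fisher's exact test, and specifies no full-scale comparison between arms

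*Protocol*

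**What the plan says.** Section 12.4 of the protocol, repeated in the Summary under Efficacy analysis, specifies for the primary outcome "a one-sided Fisher's exact test of the proportion of patients with a significant decrease in biomarker levels in the ITT (primary analysis"), with the per-protocol population as secondary analysis. It does not say which marker is meant, how large a decrease counts, or at what alpha the one-sided test is run.

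The markers are continuous. Section 9.7 says: "Serum levels of these markers will be determined using a multiplex approach with a Luminex 200 (R&Dsystems"). The schedule in section 9.6 has them drawn at days 0, 60, 120 and 360. Section 9.1 lists among its additional measures the "change in plasma levels of biomarkers of inflammation and endothelial activation".

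Section 12.4 names three further analyses: an ANOVA directed at differences between markers, exact tests for secondary comparisons of proportions, and latent class and multivariate analyses of how parasitological response, biomarker change and atorvastatin dose are associated.

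Section 12.1 plans on 75 per group, two-sided 5%, "assuming that the proportion of patients who improve electrocardiographic and echocardiographic parameters, as well as the levels of the cardiac function markers BNP and cTnT"; for atorvastatin it puts this rate, at the end of treatment, at 0.40. It adds: "The proportion in the placebo group is 0.20, with an odds ratio of 2.5". Sections 8.1 and 9.1 define the primary outcome as a change of cardiomyopathy stage.

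**The concern.** Cutting a concentration into yes or no treats a patient just past the cut like one far past it, and a patient just short of it like one who got worse. That discards information from samples the trial already plans to collect. A cut can be justified by an established clinical threshold, but the protocol offers none: the classification chart in section 9.1 defines cardiomyopathy stages, not a biomarker responder.

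A statistical analysis plan could still define the cut. It would not recover the lost information, because the protocol itself fixes the yes/no reduction and the Fisher test.

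The other analyses do not fill the gap. The ANOVA is described as a comparison between markers, not between arms. The latent class and multivariate analyses relate biomarker change to dose, but as an association that also involves parasitological response, not as a stated treatment-effect estimate. At stake is sensitivity for a mechanistic question in a proof-of-concept trial, and a result that moves with an unstated threshold.

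**Working it through.** **Inputs.** From section 12.1: rates 0.40 and 0.20, 75 per group, two-sided 5%, 25% dropout, 100 per group recruited. From section 12.4: one-sided Fisher's exact test, no alpha given. The document gives no mean change or SD for any marker, so the comparison needs an added assumption.

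**The plan's own figure.** The protocol states: "A sample size of 75 patients per group is sufficient to achieve a power of 90% at an overall significance level of 5% (2-sided"). With pooled variance, z(power) = [0.20·√75 − 1.96·√(2·0.30·0.70)] / √(0.40·0.60 + 0.20·0.80) = (1.732 − 1.270)/0.632 = 0.73, so power is 76.7%. Full enumeration of both binomials gives 71.4% for Fisher's test. The stated 90% does not reproduce; the same formula asks for 109 per group. That is a separate matter. Here the stated rates serve only to set the size of an illustrative effect.

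**Illustrative assumption.** One normally distributed change per patient with equal SD in both arms, cut so that 40% and 20% respond. The implied shift is z(0.80) − z(0.60) = 0.8416 − 0.2533 = 0.588 SD.

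**Full-scale power.** Two-sample t-test, noncentrality 0.588·√(n/2): 3.60 at n = 75 and 4.16 at n = 100.

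| Per arm | Level | Fisher on the cut | t-test on the change | Difference (points) |
|---|---|---|---|---|
| 75 | one-sided 5% | 80.9% | 97.4% | 16.5 |
| 75 | two-sided 5% | 71.4% | 94.7% | 23.3 |
| 100 | one-sided 5% | 91.0% | 99.4% | 8.4 |
| 100 | two-sided 5% | 84.4% | 98.5% | 14.1 |

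A one-sided test at 2.5% gives the same Fisher power as the two-sided rows. At 75 per arm, two-sided, 76.7 − 71.4 = 5.3 of the 23.3 points come from Fisher's conservatism rather than from the cut.

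**Dependence on the cut.** Hold the shift at 0.588 SD and 75 per arm, and move only the threshold. Two-sided Fisher power is 41%, 58%, 71% and 79% when 5%, 10%, 20% and 40% of placebo patients meet it. No cut tried between 5% and 50% exceeded 79%.

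**Other shapes giving 0.40 versus 0.20.** Simulation with 3,000 runs, 75 per arm, two-sided 5%; Fisher stays at 71.4%.

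| Shape | t-test | Wilcoxon |
|---|---|---|
| Logistic shift | 91.5% | 93.3% |
| Heavy-tailed (t, 3 df) | 73.7% | 91.3% |
| 30% of values at assay floor | 92.4% | 92.6% |
| 50% of values at assay floor | 88.6% | 90.2% |
| About 37% of patients respond, by 1.5 SD | 85.1% | 80.1% |
| About 30% respond, by 2 SD | 86.7% | 76.8% |
| About 25% respond, by 3 SD | 93.2% | 73.5% |

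At 100 per arm and one-sided 5%, where Fisher has 91.0%, the t-test under the heavy-tailed shape has 88.9%, slightly worse. Wilcoxon under the three mixtures has 91.3% to 94.8%, so little is gained.

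**The case against.** **The planning rates are not biomarker rates.** This stands. The 0.40 and 0.20 describe improvement in ECG and echocardiogram parameters together with BNP and cTnT. A reader might infer that the protocol's own assumptions imply a loss of about 20 points, or that a real effect would be missed about five times as often (28.6% versus 5.3%). The documents support neither. Both need the added normal assumption, and the second is the two-sided, 75-per-arm case only.

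**The test named is one-sided and in the ITT population.** Section 12.3 defines that as all randomized patients, up to 100 per arm, where the one-sided loss is about 8 points. This stands as the low end of the illustration. It needs a usable sample from every randomized patient, whereas section 12.1 expects 25% dropout.

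**One test must be fixed before the shape is known.** This stands. Choosing the better of t-test and Wilcoxon in each row would overstate the gain; for some shapes a single choice gains almost nothing.

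**Scope.** The Fisher sentence concerns the primary outcome, to which section 9.1 attaches only BNP and cTnT. Cytokines and adhesion molecules are secondary or additional, and section 12.4 nowhere orders them cut. A reader should not infer that every secondary marker is to be dichotomized.

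**Section 7.1.2.** Its remark that no biomarker is a gold standard concerns diagnosis. It does not show that no response threshold exists. The point rests on this protocol giving none.

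**A categorical primary outcome.** If section 12.4 were aligned with sections 8.1 and 9.1, the primary test would properly compare proportions. That is a reason to reconcile the sections. It does not supply a reason for cutting the biomarkers.

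**Conclusion.** The point holds as a matter of efficiency and clarity. Where section 12.4 and the Summary test biomarker levels between arms, they do so through an unjustified, undefined cut and state no full-scale comparison.

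The loss is roughly 16 to 23 points of power at 75 per arm and 8 to 14 points at 100 per arm (one-sided 5% to two-sided 5%). This is conditional on a single normal change with equal spread, cut at rates borrowed from a different, combined response. For heavy tails or a responding sub-group the gain ranges from nothing to substantial, depending on the full-scale test. The dependence of the result on the unstated cut remains. These figures are an illustration, not a property of the protocol's planning assumptions.

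**What to change.** Wherever section 12.4 and the Summary test biomarker levels, make the between-arm comparison (each atorvastatin arm against placebo) a linear model on log concentration, reported as a geometric mean ratio with its confidence interval. State in advance a rank-based method for markers with many values below the assay limit, and the rule for deciding which markers those are. Keep the proportion of patients with a decrease as a supportive description, with its cut defined.

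Leave categorical outcomes (cardiomyopathy stage, qPCR positive or negative) as proportions. Reconcile section 12.4 with the stage-change primary outcome in sections 8.1 and 9.1, so that it is clear which outcome each test serves.

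The cost is a change of wording, with no added patients, visits, samples or assays. The downsides are a headline less intuitive than a responder percentage and the need to handle values below the assay limit.
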